### Data management

All variables specified in the protocol will be documented on standardised paper CRFs in all participating centres. When the 6 months follow-up is done, data in the CRF of each patient will be validated for completeness, consistency and plausibility by an independent investigating physician in a local centre. Then the CRF will be transmitted to the coordinating centre (Shanghai Institute of Head Trauma), which will be responsible for the development of a central database and data entry and storage. At the end of the trial, the database will be locked and sent to the study statistician for analysis based on a predetermined statistical analysis plan.

### Statistics and data analysis

#### Sample size justification

The required sample size is calculated based on the results of our previous randomised controlled trial [24]. In that study, the proportions of patients regaining consciousness in the RMNS and non-stimulation groups were found to be 59.8% and 46.2%, respectively. Thus, to detect a difference of not less than 13.6% (the difference between 59.8% and 46.2%) between the experimental group and the control group, 334 patients will be needed with an α value of 0.05 and a power of 0.8. To allow for some patients lost to follow-up, a sample size of 380 in total (190 for each group) has therefore been chosen, which gives 84% power to detect the same difference at the same significance level.

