### Randomisation and allocation concealment

Participants at each site will be randomly assigned in a ratio of 1:1, stratified by study centre, to the stimulation group or the non-stimulation group, using a block-randomisation scheme. The whole randomisation procedure will be carried out by independent statisticians who are not involved in the determination of the final result. The trial secretary will place the computer-generated randomisation sequence and treatment assignment together into opaque envelopes and seal and mail these envelopes to each participating centre. After each patient is stabilised, assessed and identified as possibly meeting the criteria, a study physician at each local centre will do the group assignment by opening sequentially numbered envelopes.

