#### Statistical analysis

Analysis will be performed in accordance with the intention-to-treat principle. All randomised patients will be included in their original assigned group regardless of the actual treatment approach they receive. Categorical variables will be described as numbers and percentages and analysed by the chi-squared test. Normally distributed continuous variables will be presented as mean and standard deviation (SD) and compared using Student’s *t* test; non-normally distributed variables will be expressed as median and interquartile ranges and analysed using the Mann–Whitney U test. A two-sided significance level of 0.05 will be used.

Baseline data such as age and GCS score at admission will be tested for any imbalance. If imbalances are detected, those factors will be corrected using a multiple logistic regression model.

The primary endpoint, namely the percentage of patients regaining consciousness 6 months after injury, will be presented as total percentage per group and analysed as categorical variables. The secondary outcome variables describing clinical status throughout the treatment and follow-up will be analysed as continuous variables.

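### The 334 patients and the 84% power match a one-sided 5% calculation, but the plan tests two-sided at 5%: power is about 76% with 380 analysed and 70% with 334.

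*Protocol article*

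**What the plan says.** The section Sample size justification takes its rates from the group's previous trial, in which "the proportions of patients regaining consciousness in the RMNS and non-stimulation groups were found to be 59.8% and 46.2%, respectively". From the difference of 13.6 points it concludes that "334 patients will be needed with an α value of 0.05 and a power of 0.8". It then raises the total to 380, 190 per group, to cover loss to follow-up. Of this larger total it says: "which gives 84% power to detect the same difference at the same significance level". The paragraph does not say whether α is one-sided or two-sided, and it gives no loss rate.

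The section Statistical analysis settles the test. "Categorical variables will be described as numbers and percentages and analysed by the chi-squared test", the primary endpoint is to be analysed as categorical, and "A two-sided significance level of 0.05 will be used". Allocation is 1:1 (Randomisation and allocation concealment). No section mentions a one-sided test.

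**The concern.** A difference of 13.6 points around a rate of about 53% should need more than 400 patients for 80% power in a two-sided 5% test, so 334 looks too low. If the figures come from a one-sided calculation, the trial has less power for its primary endpoint than it claims.

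A second point lies in the same sentence. The step from 334 to 380 is there to absorb losses, yet the 84% is the power with all 380 analysed. The 46 additional patients cannot both replace those lost and add power.

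The Background presents an adequate sample size as the answer to the weaknesses of earlier studies. A neutral result would then be read as stronger evidence against the treatment than the design supports.

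**Working it through.** **Inputs** (Sample size justification, Statistical analysis, Randomisation): p1 = 0.598, p2 = 0.462, d = 0.136, d² = 0.018496, mean rate p̄ = 0.530, 1:1 allocation, α = 0.05, target power 0.80 (z = 0.8416).

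Variance terms: V0 = 2p̄(1 − p̄) = 0.4982, √V0 = 0.7058; V1 = p1(1 − p1) + p2(1 − p2) = 0.48895, √V1 = 0.6993.

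**Formulas.** n per group = (zα√V0 + zβ√V1)² / d². Power = Φ[(d√n − zα√V0) / √V1].

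**Step 1: reproduce the printed figures.** With one-sided α = 0.05, zα = 1.6449.
- n = (1.1610 + 0.5885)² / 0.018496 = 165.5, so 166 per group, 332 in total.
- With V0 in both terms, n = (1.6449 + 0.8416)² × 0.4982 / 0.018496 = 166.5, so 167 per group: exactly 334. The same version gives 84.4% power at 190 per group. One simple one-sided formula thus returns both printed figures.
- The standard formula gives one-sided power of 80.3% at 334 and 84.6% at 380.

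**Step 2: apply the stated two-sided test.** zα = 1.9600.
- n = (1.3834 + 0.5885)² / 0.018496 = 210.2, so 211 per group, 422 in total.
- Power at 190 per group: d√n = 1.8746; (1.8746 − 1.3834) / 0.6993 = 0.7025; Φ = 75.9%.
- Power at 167 per group: d√n = 1.7575; (1.7575 − 1.3834) / 0.6993 = 0.5350; Φ = 70.4%.
- 84% power would need 234 per group, 468 in total.

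**Step 3: could another two-sided method give 334?**

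| Two-sided 5%, 80% power | Total |
|---|---|
| Unpooled variance | 416 |
| Standard formula (Step 2) | 422 |
| Arcsine | 422 |
| Pooled variance in both terms | 424 |
| Continuity-corrected | 450 |

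None is near 334. Rounding in the two input rates moves the standard result only between 416 and 428.

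**Step 4: exact check.** Enumerating the binomial distributions for the uncorrected two-sided chi-squared test gives 75.1% at 380 and 71.8% at 334. With a continuity correction it gives about 72% and 68%.

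**Step 5: loss.** 1 − 334/380 = 46/380 = 12.1%. This rate is implied by the two totals, not stated.

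**Step 6: detectable difference.** Solving the two-sided power formula for 80% from a control rate of 46.2% gives 14.3 points with 380 analysed and 15.2 points with 334, against the 13.6 claimed.

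**The case against.** The case against does not dispute the core arithmetic, but it makes several fair points.

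- **The one-sided origin is inferred.** The sample size paragraph is silent on sidedness. That stands, but the error does not depend on it: under the only test the article specifies, 334 and 84% are wrong however they arose.
- **The 84% may be a full intention-to-treat figure.** The article says that all randomised patients are included, and handling of lost patients can be left to the analysis plan. So 84% may be meant as the power with complete data. Even then it is about 76% two-sided. The sentence still credits patients added for loss with extra power and does not separate recruited from evaluable numbers.
- **The 70% rests on an assumed loss.** This stands. It is the power if 334 are evaluable, and the exact value there is slightly higher, 71.8%.
- **Recruitment could be raised instead.** The trial was still recruiting, so 422 analysed patients would restore 80% power. That is a valid alternative, but not a cheap one.
- **The type I error and the treatment comparison are untouched.** True, and against the 80% target the shortfall with all 380 analysed is only about 4 points. It remains a misstated design figure for the primary endpoint.

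**Conclusion.** The concern holds. The sample size paragraph and the two-sided 5% test in the next section cannot both be right. For the planned rates, a two-sided test needs 422 analysed patients for 80% power, 88 more than the 334 stated. Power is 75.9% with 380 analysed (exact 75.1%) and 70.4% with 334 (exact 71.8%). The risk of a false-negative result at the planned effect is therefore about 24% with no loss and about 28% to 30% with 334 evaluable, against the 16% to 20% implied.

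These values assume the article's own rates, equal groups and an uncorrected chi-squared test; a continuity correction would lower power further. The lower value also assumes the 12.1% loss implied by 334/380.

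**What to change.** Keep 380 and replace the two power claims with a statement such as: *With a two-sided α of 0.05, 380 analysed patients give 76% power, and 334 evaluable patients (12% loss, assumed) give 70% power, for 59.8% against 46.2%. The difference detectable with 80% power from a control rate of 46.2% is 14.3 points with 380 and 15.2 points with 334.* Give the recruited number and the evaluable number after loss as separate figures, and name the assumed loss rate. Do not change the test to one-sided to recover the printed figures.

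This costs wording only and no extra patients; the stated power becomes less favourable. If the sponsor prefers to hold the 80% target, the requirement is 422 analysed patients, or about 481 randomised at the implied loss (422 / 0.879 = 480.1). That is about 101 more than planned.

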#### Statistical analysis

Analysis will be performed in accordance with the intention-to-treat principle. All randomised patients will be included in their original assigned group regardless of the actual treatment approach they receive. Categorical variables will be described as numbers and percentages and analysed by the chi-squared test. Normally distributed continuous variables will be presented as mean and standard deviation (SD) and compared using Student’s *t* test; non-normally distributed variables will be expressed as median and interquartile ranges and analysed using the Mann–Whitney U test. A two-sided significance level of 0.05 will be used.

Baseline data such as age and GCS score at admission will be tested for any imbalance. If imbalances are detected, those factors will be corrected using a multiple logistic regression model.

The primary endpoint, namely the percentage of patients regaining consciousness 6 months after injury, will be presented as total percentage per group and analysed as categorical variables. The secondary outcome variables describing clinical status throughout the treatment and follow-up will be analysed as continuous variables.

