### Study settings and population

A total of 380 patients will be recruited from 16 large, experienced, specialised neurosurgical centres across Asia: (1) Shanghai Renji Hospital; (2) Guangzhou General Hospital of Guangzhou Military Region; (3) the People’s Hospital of Shaoxin, Zhejiang; (4) the 98 Hospital of the People’s Liberation Army; (5) the Second People’s Hospital of Nanning, Guangxi; (6) the Central People’s Hospital of Tengzhou, Shandong; (7) Harrison International Peace Hospital of Hengshui, Hebei; (8) the 421 Hospital of the People’s Liberation Army; (9) Jiangning Hospital of Nanjing, Jiangsu; (10) the First People’s Hospital of Yulin, Guangxi; (11) the First People’s Hospital of Huaian, Jiangsu; (12) the People’s Hospital of Hunan; (13) the People’s Hospital of Pingyang, Zhejiang; (14) the Second People’s Hospital of Tianshui, Gansu; (15) the Fifth People’s Hospital of Zhengzhou University; (16) General Hospital of Beijing Military Region.

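### Randomisation is stratified by 16 centres, but the primary chi-squared test has no centre term; if centres differ in recovery, the test is conservative and forgoes some power

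*Protocol article*

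**What the plan says.** Under Randomisation and allocation concealment, the Protocol article states "Participants at each site will be randomly assigned in a ratio of 1:1, stratified by study centre", with a block scheme. Under Study settings and population it states "A total of 380 patients will be recruited from 16 large, experienced, specialised neurosurgical centres across Asia", which is 380/16 = 23.75 patients per centre on average.

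Under Statistical analysis, the general rule is "Categorical variables will be described as numbers and percentages and analysed by the chi-squared test". The primary endpoint "will be presented as total percentage per group and analysed as categorical variables". The only adjustment foreseen concerns baseline variables, with age and admission GCS score as examples: "If imbalances are detected, those factors will be corrected using a multiple logistic regression model". Centre is not mentioned anywhere in the analysis text.

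The Data management section refers to a predetermined statistical analysis plan, which is not shown.

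**The concern.** Blocking within centre keeps the two arms nearly equal in every hospital, so differences in recovery between hospitals largely cancel out of the treatment comparison. The pooled chi-squared test does not know this. Its variance still includes the between-centre part, as if centre balance had been left to chance. Where centres differ, the standard error used is therefore larger than the true one, the p-value is too high on average, and the actual type I error lies below the nominal 5%.

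The adjustment clause would not be expected to correct this. It is triggered by imbalance between arms, and stratified blocks are there to prevent imbalance by centre. The balance that keeps centre out of the model is also what makes the pooled standard error too large.

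At stake are efficiency and calibration on the primary endpoint: a real effect could narrowly miss significance in a test that does not use the design.

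**Working it through.** **Inputs.** Rates of 59.8% and 46.2% (Sample size justification: "the proportions of patients regaining consciousness in the RMNS and non-stimulation groups were found to be 59.8% and 46.2%, respectively"). 190 patients per arm, 16 centres, two-sided 0.05 (Statistical analysis). Assumed, because the document gives neither: normally distributed centre effects on the logit scale with SD 0 to 1.0, and blocks of 4 or 8.

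**Step 1: the plan's own figures.** The section states "334 patients will be needed with an α value of 0.05 and a power of 0.8", and 84% power with 380. Mean rate = (0.598 + 0.462)/2 = 0.53.
- SE under the null: √(2 × 0.53 × 0.47/190) = 0.0512.
- SE under the alternative: √((0.598 × 0.402 + 0.462 × 0.538)/190) = 0.0507.
- Two-sided power: Φ((0.136 − 1.96 × 0.0512)/0.0507) = Φ(0.702) = 75.9%.
- One-sided power: Φ((0.136 − 1.645 × 0.0512)/0.0507) = 84.6%.

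The stated 84% is approached only one-sided. The same holds for the 334: the formula gives 332 one-sided and 422 two-sided. That is a separate issue. The reference value here is the two-sided 75.9%.

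**Step 2: what ignoring centre does, in closed form.** Let ρ be the share of outcome variance that lies between centres. With balance within centre, the true SE is about √(1 − ρ) times the SE the pooled test uses. Then:
- actual type I error of chi-squared ≈ 2 × [1 − Φ(1.96/√(1 − ρ))];
- power of chi-squared ≈ Φ(0.702/√(1 − ρ));
- power of a stratified test ≈ Φ((0.136 − 1.96 × 0.0512 × √(1 − ρ))/(0.0507 × √(1 − ρ))).

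| Centre SD (logit) | ρ | Type I, chi-squared | Power, chi-squared | Power, stratified |
|---|---|---|---|---|
| 0 | 0 | 5.0% | 75.9% | 75.9% |
| 0.25 | 0.015 | 4.8% | 76.0% | 76.5% |
| 0.5 | 0.056 | 4.4% | 76.5% | 78.3% |
| 0.8 | 0.123 | 3.6% | 77.3% | 81.2% |
| 1.0 | 0.173 | 3.1% | 78.0% | 83.4% |

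**Step 3: simulation.** Uncorrected chi-squared against Cochran-Mantel-Haenszel (CMH) by centre, marginal rates held at 59.8% and 46.2%. All rows except SD 0.8: N = 380, blocks of 4, 100,000 trials. SD 0.8: N = 384 (12 per arm per centre), 6,000 trials.

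| Centre SD | Type I, chi-squared / CMH | Power, chi-squared / CMH |
|---|---|---|
| 0 | 4.9% / 5.0% | 75.4% / 75.8% |
| 0.25 | 4.7% / 5.1% | 75.8% / 76.8% |
| 0.5 | 4.2% / 4.9% | 76.2% / 78.3% |
| 0.8 | 3.5% / 5.4% | 76.8% / 80.9% |
| 1.0 | 3.1% / 5.0% | 77.7% / 83.2% |

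A further run of 40,000 trials at SD 0.8 gave power of 77.5% against 81.8%. Blocks of 8 gave nearly the same figures, and unequal centre sizes gave the same direction. Closed form and simulation agree to within about a point.

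**The case against.** **The size rests on an assumption.** This stands. The documents report no variation between centres. They describe large specialised hospitals with common eligibility criteria and guideline-based care, which argues against extreme spread. Around a 50% rate, an SD of 1.0 puts the middle 95% of centres between about 12% and 88% recovery, and an SD of 0.8 between about 17% and 83%. At SD 0.25 the gain is about one point. If only 334 patients were evaluable, the simulation showed no loss from chi-squared at SD 0.25 or below (for example 71.7% against 71.1% at 0.25).

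**A reader might infer that the trial loses power it was counting on.** The documents do not support that. The sample-size calculation itself compares two crude proportions, so the chi-squared test matches its basis. Simulated chi-squared power stays at about the 75.9% formula value and rises slightly as centres diverge. What is given up is a gain that another analysis would bring.

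**A reader might also link this to the gap between the stated 84% and about 76%.** That gap comes from one-sided planning against a two-sided test. It adds no weight to this point, and the stratified test reaches 84% in none of the settings above.

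**A reader might call the chi-squared test invalid.** It is not. Its error is on the safe side, and a significant result would remain credible.

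**The unseen analysis plan may already stratify, and the chi-squared sentence is generic.** This lowers certainty somewhat. However, the article does not leave the test open: it names one and describes the primary endpoint as a total percentage per group. An analysis plan that adds centre would depart from the published text, so the two would need reconciling.

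**Conclusion.** The point holds as one of efficiency and calibration. The protocol fixes a primary test that ignores the factor its randomisation is stratified by. The consequence is conditional on centres differing in recovery rate. Across assumed logit-scale SDs of 0, 0.25, 0.5, 0.8 and 1.0, a centre-stratified test would gain about 0, 1, 2, 4 and 5 to 6 points of power. The chi-squared type I error would be about 5, 4.7, 4.2, 3.5 and 3.1%, against about 5% for the stratified test.

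At low to moderate variation the gain is therefore 0 to 2 points, and it is larger only if centres differ a great deal. The figures assume the planning rates, 16 centres and all 380 patients analysed. The change is worth making because it costs almost nothing, not because the present test endangers the trial's conclusions.

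**What to change.** Before database lock, state in the protocol and the analysis plan that:
- the primary test is a two-sided CMH test stratified by centre;
- the effect estimate is a centre-stratified (Mantel-Haenszel) risk difference with 95% CI, which keeps the scale on which the sample size was set; logistic regression with centre would instead estimate a conditional odds ratio;
- very small centres are pooled by a rule written down before the data are seen by arm;
- the crude percentages and the chi-squared test are reported as descriptive.

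If the analysis plan already stratifies by centre, align the protocol wording with it. The cost is analysis wording only: no extra patients, visits or data items, since centre is known for everyone. The mismatch between the stated 84% power and the two-sided test needs its own correction.

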### Data collection and follow-up

General baseline information will be collected about patients when they are sent to the emergency room and will include the following: demographics, time of admission, cause of injury, whether accompanied by multiple trauma, injury severity score, initial GCS score, initial intracranial computed tomography (CT) data including Marshall score and whether complicated by subarachnoid haemorrhage, pupillary light reflex or the need of craniotomy.

After 7–14 days of standard treatment, when the patient’s condition is stable and once he/she is enrolled and randomised, additional data will be collected, including vital signs such as blood pressure, heart rate, respiratory rate and oxygen saturation, pupillary light reflex and GCS, FOUR, CRS-R and DRS scores.

Patients in both the RMNS group and the sham group will be evaluated via GCS and FOUR scores at day 1 and day 7 of the treatment. Whether or not the coma patient regains consciousness and the date will be recorded in the CRF. Any complications will also be observed and recorded during the treatment.

Outcome assessment will be performed using the GCS, FOUR, CRS-R, DRS and GOSE at 1, 3 and 6 months. Complications during follow-up will also be assessed. If the patient is still in the hospital, the investigator may visit the patient on the ward to go through the evaluation. If the patient has been discharged, his or her legal representative will be told to come back in due time for assessment after leaving the hospital. If the patient does not arrive, the investigator will try to contact the patient or the family members by telephone. Other possible methods may also be used to explain the situation and complete the outcome assessment. If all attempts fail, no further contact will be made, and the patient will be recorded as lost to follow-up. Any death occurring either in or out of the hospital will be recorded and possible causes explored.

All the data will be collected by independent investigators who are blind to the patient’s allocation. Each local study centre will assign a specific investigator at the beginning of the trial. This investigator will be excluded throughout treatment of all the participants unless asked to do the assessment by clinicians. During the 2 weeks of RMNS treatment, the investigators will be asked to collect the data during the interval of 8-h RMNS treatment per day so as to eliminate any chance of disclosing the allocation.

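### Covariate adjustment is made conditional on baseline imbalance tests, which forgoes power and leaves the effect measure open until the baseline data are seen

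*Protocol article*

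**What the plan says.** All the rules sit in the protocol article under Statistical analysis.

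- **Default.** "Categorical variables will be described as numbers and percentages and analysed by the chi-squared test". The primary endpoint, regaining consciousness by 6 months, "will be presented as total percentage per group and analysed as categorical variables". Read together, these make an unadjusted chi-squared test the default.
- **Trigger.** "Baseline data such as age and GCS score at admission will be tested for any imbalance". The list of variables is given by example only.
- **Consequence.** "If imbalances are detected, those factors will be corrected using a multiple logistic regression model". Only factors found to differ enter the model.
- **Level.** "A two-sided significance level of 0.05 will be used". No separate threshold is given for calling a baseline difference an imbalance.

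Randomisation is 1:1 in blocks, stratified by centre (Randomisation and allocation concealment). Data collection and follow-up lists emergency-room data, including initial GCS and Marshall score. It also lists a second set taken at enrolment after 7 to 14 days of standard care, including "pupillary light reflex and GCS, FOUR, CRS-R and DRS scores". Data management refers to a predetermined statistical analysis plan, which is not shown.

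**The concern.** Allocation is random, so a baseline difference between arms is chance by construction, and testing for it answers no useful question. The reason to adjust is that a covariate predicts outcome, and an imbalance test does not measure that. A strongly prognostic variable that happens to be balanced is left out, and an irrelevant one that happens to differ is put in.

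Two things are at stake. One is power: adjusting for prognostic baselines helps in every trial, not only in those with a visible imbalance. The other is the effect measure. The default gives a difference in percentages, and the logistic model gives an odds ratio conditional on whichever factors were flagged. These are different quantities, and the rule lets the baseline table decide which one is obtained.

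**Working it through.** **Inputs from the document.** The rates regaining consciousness in the earlier trial "were found to be 59.8% and 46.2%, respectively" (stimulation, control). The sample size statement is that "334 patients will be needed with an α value of 0.05 and a power of 0.8", raised to 190 per arm with a stated power of 84%. The analysis is two-sided at 0.05.

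**Assumed.** A 0.05 trigger for each baseline test; independent tests; full follow-up; covariate strength, shown as a range.

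**Step 1: the plan's own figures.** With pooled variance and no continuity correction,

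n per arm = [z_α √(2p̄(1−p̄)) + z_β √(p₁(1−p₁) + p₂(1−p₂))]² / (p₁−p₂)².

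Here p̄ = 0.530, √(2 × 0.530 × 0.470) = 0.706, √(0.2404 + 0.2486) = 0.699 and the difference is 0.136.

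- One-sided 0.05: [1.645 × 0.706 + 0.842 × 0.699]² / 0.0185 gives 166 per arm, 332 in total (stated 334). Power at 190 per arm is 84.6% (stated 84%).
- Two-sided 0.05: 211 per arm, 422 in total. Power at 190 per arm is Φ[(0.136 × √190 − 1.960 × 0.706) / 0.699] = Φ(0.70) = 75.9%.

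The stated figures therefore match a one-sided calculation. That is a separate issue, but it sets the reference: an unadjusted two-sided test has about 76% power, some 8 points below the stated 84%.

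**Step 2: how often the trigger leaves a factor out.** Each test at 0.05 is non-significant in 95% of randomised trials.

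- One factor: omitted in 95%.
- Two factors (for instance age and GCS): neither flagged in 0.95² = 90.25%.
- Five factors: none flagged in 0.95⁵ = 77%.
- Ten factors: none flagged in 0.95¹⁰ = 60%.

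Testing more variables makes it likelier that something is flagged, but any particular prognostic factor is still omitted in 95%.

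**Step 3: power under the three strategies.** Simulated trials, 190 per arm, marginal rates fixed at 46.2% and 59.8%, two-sided 0.05, one prognostic covariate. Strength is the standard deviation of its contribution to the log-odds; 0.8, 1.2 and 1.6 correspond to an AUC of about 0.70, 0.77 and 0.82.

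| Log-odds SD (assumed) | Chi-squared or triggered rule | Pre-specified adjustment |
|---|---|---|
| 0.3 to 0.5 | 74–78% | about 78% |
| 0.8 | 74–78% | 81–83% |
| 1.2 | 74–78% | 86% |
| 1.6 | 74–78% | 89–90% |

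Unadjusted power does not depend on covariate strength once the marginal rates are fixed, so the spread in the middle column is mainly simulation error around 75.9%. With 4,000 trials the standard error is √(0.76 × 0.24 / 4000), or 0.7 points.

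A version with two independent covariates (6,000 trials per scenario), with log-odds slopes of 0.5, 0.8 and 1.0 per SD each, agrees:

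- chi-squared: 74.3%, 76.2%, 74.9%
- triggered rule: 75.0%, 76.9%, 76.2%
- pre-specified adjustment: 79.7%, 84.7%, 87.7%

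The triggered rule gains about 1 point (0.6 to 1.3). Always adjusting gains about 5 to 13.

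**Step 4: type I error.** Under no effect the triggered rule rejects in 4.1% to 4.7% of trials. Pre-specified adjustment rejects in 4.9% to 5.1%.

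**Step 5: the effect measure.** The planning rates imply an unadjusted odds ratio of (0.598/0.402) / (0.462/0.538) = 1.73. In the two-covariate scenarios the conditional odds ratio behind the same 13.6-point difference is 1.84, 1.99 and 2.13. The number reported thus changes with the covariates that enter, even though the effect on percentages does not.

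**The case against.** Several points on the other side stand.

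- **Validity.** A reader might infer that choosing the model after seeing data inflates false positives. The document does not support that. The trigger uses baseline data, not outcomes, and the rule keeps type I error slightly below nominal. Inflation to 6.2% to 7.6% would arise only if both analyses were run and the better one reported, and nothing says this will be done.
- **Which analysis is primary.** A reader might infer that the logistic model replaces the chi-squared test. The imbalance paragraph does not name the primary endpoint and could describe a supportive analysis. Consciousness at 6 months is the only binary efficacy endpoint named, so the rule most naturally falls on it, but the text does not settle this.
- **Size of the gain.** A reader might infer that adjustment would make up the whole power shortfall. For weak covariates the gain is only 1 to 3 points. Entry is limited to GCS 4–8 or motor score below 5, ages 18 to 65 and stable vital signs, which may narrow the prognostic spread. The simulations also assume full follow-up and a correctly specified model, and do not include 16 centres.
- **Admission GCS.** A reader might infer that the plan commits to the wrong baseline. Admission GCS is only an example, and nothing excludes the scores taken at enrolment.
- **Left to the SAP.** The covariate list and the threshold may properly be set there. The conditional rule itself is not left open: the protocol states it, and an SAP that followed the protocol would inherit it.

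**Conclusion.** The rule is badly fixed and should be changed, but it does not make the planned analysis invalid. With a 0.05 trigger it leaves any given prognostic factor out in about 95% of trials, so it performs almost like no adjustment: about 74% to 78% power either way. Pre-specified adjustment would give about 78% to 90% over the range of strengths considered. It passes the stated 84% only when the baselines are fairly strong (86% at a log-odds SD of 1.2, but 81% to 83% at 0.8). Part or all of the gap may be recovered, and neither is assured.

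The second harm does not depend on prognostic strength: the effect measure and its covariates are not determined in advance. The conclusion rests on the assumed 0.05 trigger and on reading the rule as applying to the primary endpoint. The power figures also rest on assumed covariate strength, for which the document gives no figure.

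**What to change.** Delete the baseline significance tests and the conditional rule; describe baseline data by arm without p-values. Pre-specify one primary logistic analysis, used whatever the baseline table shows, with:

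- treatment;
- centre, as the randomisation stratum, with small centres pooled or centre fitted as a random effect;
- a short fixed list of baselines already collected, such as age and GCS or CRS-R at randomisation.

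Report the adjusted odds ratio together with a standardised risk difference, each with a 95% confidence interval. Keep the unadjusted chi-squared comparison as supportive.

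The cost is a change of wording, slightly more analysis work, and advance rules for small centres and missing baseline values. No new data or patients are needed.
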